## Abstract

**Introduction:**

As the presence of hepatic metastases is very important to cancer patients' clinical stage which would directly affect the selection and application of anti-cancer treatments. Although conventional ultrasound is commonly performed as a screening tool, most of the examinations have relatively poor sensitivity and specificity for detecting liver metastases. Contrast-enhanced ultrasound (CEUS) with Sonazoid has been reported to have the advantage of the diagnosis and therapeutic support of focal hepatic lesions and its specific Kupffer phase whole liver scan (KPWLS) is believed to be sensitive to detect liver metastases. And the purpose of this study is to determine the number, size, location and diagnosis of metastatic lesions, and to compare the results with conventional ultrasound and contrast-enhanced computed tomography (CECT), thus to clarify the application value, indications of Sonazoid-CEUS in screening liver metastasis.

**Methods and analysis:**

Kupffer phase whole liver scan for metastases (KPWLSM) is a self-control, blind map-reading, single-center, prospective superiority trial. Approved by the institutional review committee, the study period is planned to be from 1 January 2022 to 31 December 2025. Our study will include 330 patients with history of malignant tumors that cling to metastasize to liver. All patients will undergo the examinations of conventional ultrasound, Sonazoid-CEUS, and contrast-enhanced magnetic resonance imaging (CEMRI), and 65 of them should have additional CECT scans. The primary endpoint is the comparative analysis of the numbers of detected liver metastatic lesions among Sonazoid-CEUS, conventional ultrasound and CECT in screening liver metastases. Subjective conditions of patient after injection of Sonazoid will be followed up 3 and 30 days after KPWLSM, and any short-term and long-term adverse events are to be recorded with telephone interviews.

**Ethics and dissemination:**

This study has been granted by the Ethics Committee of Shanghai Jiao Tong University Affiliated Sixth People's Hospital (Approval No: 2021-197). When the KPWLSM is completed, we will publish it in an appropriate journal to promote further widespread use.

**Registration:**

Trial Registration Number and Date of Registration: Chinese Clinical Trial Registry, ChiCTR2100054385, December 16, 2021.

## Introduction

Liver is one of the most common sites for malignant tumor metastasis, and the presence, number, size, location and main adjacent relationship of hepatic metastases are crucial to the patient's clinical stage and the selection of overall treatment plan. Therefore, imaging examination of liver is very important for preoperative patients highly suspected with malignant tumor and in postoperative follow-up of patients with cancer that cling to metastasize to liver.

Contrast-enhanced US (CEUS) has been demonstrated as a suitable imaging technique because of higher spatial resolution and higher safety of microbubble contrast agents (1). Sonazoid (GE Healthcare, Oslo, Norway) is a highly specific mononuclear phagocytosis (MPS) US contrast agent which consists of perfuorobutane gas stabilized by a monomolecular membrane of hydrogenated egg phosphatidylserine (2). Sonazoid has been applied in various clinical practice including the diagnosis of focal liver lesions (3–5) and guidance of surgical or radiological interventions (6–8).

Traditional Sonovue ultrasound contrast agent has three vascular phases: arterial phase (10–40 s after intravenous administration), portal venous phase (60–90 s), and delay phase (3 min), and sonographers can observe the target lesion in these three phases in only 5 min. While Sonazoid contrast agents could be swallowed by macrophages of the liver (Kupffer cells), allowing for continuous imaging, which can last more than 1 h with high stability, then the sonographers could have sufficient time for a whole liver scan. In the Kupffer phase, malignant tumor, especially metastatic tumor will be present as a well-defined filling defect due to the lack of Kupffer cells which could be easily observed by the sonographer.

Although several studies have investigated the diagnostic performance of CEUS in liver metastasis, large heterogeneity is noted in their study results: such as sensitivity of 73–98.8%, specificity of 44.4–99.0%, different standards of reference (histology, magnetic resonance imaging (MRI), follow-up computed tomography (CT) and clinical follow-up), and inhomogeneous cohorts, etc. (9–12).

Besides, as Sonazoid became clinically available in April 2019 in China after prospective Phase 3 study conducted from May 2014 to April 2015 (13). A large-cohort and prospective study is still necessary to further explore the efficacy and indications of contrast Sonazoid-enhanced ultrasonography for the detection of hepatic metastases.

However, it is still unclear whether patients with malignant tumor truly benefit from KPWLS in terms of the detection of liver metastasis. We wonder whether it could be used as a screening tool for postoperative patients with malignant tumor to avoid unnecessary additional examinations such as contrast-enhanced computed tomography (CECT). And the purpose of this study is to determine the number, size and location of metastatic lesions, and to compare the results with conventional ultrasound and CECT, thus to clarify the application value, indications of Sonazoid CEUS in screening liver metastasis. We will also analyze how influential factors such as position, echogenity and other unknown factors restrict the use of Sonazoid CEUS and explore how to improve it.

## Methods and analysis

### Design

To make the study design more clear, we made a brief **PICOT** as follows:

### P (patient, population or problem)

Our study will include 330 patients with the history of malignant tumors prone to liver metastasis who visit the Shanghai Jiao Tong University Affiliated Sixth People's Hospital during this study period.

### I (intervention)

All patients will receive the examinations of Sonazoid-CEUS, conventional ultrasound and contrast-enhanced MRI (CEMRI), and 65 of them should have additional CECT scans.

### C (comparison or control)

Kupffer phase whole liver scan for metastases (KPWLSM) is a self-control, blind map-reading, single-center, prospective superiority trial. We set Sonazoid-CEUS, and CECT as the test group, and conventional ultrasound as the control group.

### O (outcome or objective)

The primary endpoint is the comparative analysis of the numbers of detected liver metastatic lesions among KPWLS in Sonazoid-CEUS, conventional ultrasound and CECT in screening liver metastases. The secondary endpoint is the comparative analysis of diagnostic accuracy between Sonazoid-CEUS and CECT in a single lesion. Subjective conditions of patient after injection of Sonazoid will be followed up 3 and 30 days after KPWLSM, and any short-term and long-term adverse events are to be recorded with telephone interviews. The study flow diagram is presented in Figure 1.

**Figure 1 F1:**
[figure not shown]
The study flow diagram. *Either radiological or ultrasound examination start first is OK.

### T (time frame)

Approved by the institutional review committee, the study period is planned to be from 1 January 2022 to 31 December 2023.

### Study participants

#### Inclusion criteria

Inclusion criteria (must meet ①, ②, ③ and ④)

① The history of malignant tumors prone to liver metastasis (with or without specific liver metastasis, mainly non-epigastric malignancies);

② have done or plan to have a CEMRI examination within 2 months;

③ Age 18–75 y;

④ have done or plan to have a CECT examination within 2 months (optional, but at least 65 patients should finish it).

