#### Exclusion criteria

① Patients with liver metastases after local treatment such as ablation or transcatheter arterial chemoembolization;

② Patients with a history of allergy to egg or any type of ultrasound contrast agent;

③ Pregnant or lactating women;

④ Reluctant to perform contrast-enhanced ultrasound examination;

⑤ Severe heart disease, hypertension, severe liver and kidney dysfunction;

⑥ Pulmonary dysfunction;

⑦ Other conditions that are not suitable for ultrasound examination or enhanced CT/MRI examination.

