#### Primary endpoint

The primary study endpoint is the comparative analysis of the number of detected liver metastatic lesions among Sonazoid-CEUS, conventional ultrasound and CECT in screening liver metastases. If the results show that Sonazoid-CEUS could detect more lesion than conventional ultrasound and CECT, the study will be considered to be successful because it means the data collected in the present study confirmed the diagnostic improvement provided by Sonazoid-CEUS over conventional ultrasound and CECT, Sonazoid-CEUS will be confirmed as an excellent screening tool without radiation exposure.

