Reference diagnosis of our study is inevitably heterogeneous. Histopathological results will be obtained in some cases which is the strongest evidence of suspected lesions. However, not all enrolled patients will accept surgical resection or biopsy, in part of the cases may be based on comprehensive clinical assessment including CEMRI, clinical or laboratory indicators. A preferred 1-year follow-up will be performed to confirm the reference diagnosis in the controversial lesion.

KPWLSM is the first domestic large-sample study to investigate the diagnostic efficacy of Sonazoid-enhanced ultrasonography in screening liver metastasis among cancer patients. KPWLSM will provide strong evidence regarding whether patients with a tentative diagnosis of liver metastasis could truly benefit from Sonazoid-enhanced ultrasonography in terms of the detection of early liver metastasis while avoiding additional unnecessary MRI or CT.

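### The success rule turns a pooled lesion count into a screening claim, although patients with known untreated liver metastases may enter and nothing ties the claim to identifying which patients have metastases.

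*Protocol article*

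**What the plan says.** **Intended use.** The Introduction of the protocol article states: "We wonder whether it could be used as a screening tool for postoperative patients with malignant tumor". It then gives the study's purpose as describing how many metastatic lesions there are, how large and where, against conventional ultrasound and CECT.

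**Who enters.** Inclusion criterion 1 is "The history of malignant tumors prone to liver metastasis (with or without specific liver metastasis, mainly non-epigastric malignancies". Criterion 2 is "have done or plan to have a CEMRI examination within 2 months", so the liver may already have been imaged at entry. The only exclusion that concerns existing metastases is "Patients with liver metastases after local treatment such as ablation or transcatheter arterial chemoembolization".

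**What is counted.** "The primary study endpoint is the comparative analysis of the number of detected liver metastatic lesions among Sonazoid-CEUS, conventional ultrasound and CECT". Under Data analysis, lesion numbers are compared within patients by a paired t-test.

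**What follows.** "If the results show that Sonazoid-CEUS could detect more lesion than conventional ultrasound and CECT, the study will be considered to be successful", and in the same sentence "Sonazoid-CEUS will be confirmed as an excellent screening tool without radiation exposure".

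**Other measures.** Data analysis also lists sensitivity, specificity, the two predictive values and accuracy, with a chi-square or Fisher test across the three modalities. It does not say whether the unit is the patient or the lesion, and the success rule does not use these measures. The secondary endpoint compares CEUS with CECT on a single lesion.

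**The concern.** Screening asks whether a patient not known to have liver metastases has any. A lesion count answers a different question. Finding eight lesions rather than six in a patient already known to be positive adds two to the primary endpoint, but that patient is classified exactly as before.

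Entry allows such patients, the count pools them with everyone else, and the protocol fixes in advance that a higher count confirms a screening tool. A reader of the final report could then be told that CEUS is proven for screening when the evidence concerns how many lesions are seen in patients with disease. The Discussion goes further and suggests that CT or MRI could be avoided.

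**Working it through.** **1. Where the primary result comes from.** A patient without metastases has no true metastatic lesion, so every modality scores zero true lesions and the within-patient difference is zero. The true-lesion difference therefore comes wholly from patients with metastases, known or new. A patient with *k* lesions can contribute up to *k* to it. The patient-level question gives each patient one yes or no.

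**2. Lesion gain against patient gain.** Inputs: 99 lesions in 27 patients (series cited in the Discussion), and the low-end sensitivities under Sample size, 62.5% for conventional ultrasound and 73% for CEUS. Assumptions: the sensitivities apply per lesion, and detections are independent.

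- Mean lesions per patient: 99/27 = 3.67.
- Extra lesions per patient: 3.67 × (0.73 − 0.625) = 0.39. Relative gain: 0.73/0.625 = 1.17, or 17%.
- At least one lesion found, if every patient had 3.67 lesions, is 1 − (1 − s)^3.67. Ultrasound: 1 − 0.375^3.67 = 97.3%. CEUS: 1 − 0.27^3.67 = 99.2%. Gain 1.9 points.
- Same mean with a geometric spread, p = 27/99 = 0.273 and q = 1 − s: 1 − pq/[1 − (1 − p)q]. Ultrasound: 1 − 0.1023/0.7273 = 85.9%. CEUS: 1 − 0.0736/0.8036 = 90.8%. Gain 4.9 points.
- One lesion per patient: gain 10.5 points.

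The same 17% lesion gain thus goes with a patient-level gain of 1.9, 4.9 or 10.5 points, depending on how lesions are spread over patients. The count alone does not tell these apart.

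**3. Can the test favour CEUS with no patient-level gain?** The planned paired t-test (two-sided 5%) was simulated with 330 × 0.9 = 297 evaluable patients and 2,000 trials per setting. Both methods always find the first lesion of a positive patient, and there are no false positives, so they classify every patient identically. Additional lesions follow a Poisson distribution. Ultrasound finds 62.5% of them; CEUS finds 73%, or an assumed 82.5%. The stated 25–50% prevalence is read as the share of positive patients.

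| Positive patients | Mean additional lesions | Test favours CEUS, 73% | Test favours CEUS, 82.5% |
|---|---|---|---|
| 25% | 1 | 28% | 77% |
| 25% | 2 | 47% | 96% |
| 25% | 3 | 63% | 99.5% |
| 50% | 1 | 48% | 97% |
| 50% | 2 | 77% | 99.9% |
| 50% | 3 | 92% | 100% |

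Patient-level gain is zero in every row by construction. The simulation does not separate known from newly found positives.

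**4. What this does not cover.** The rule also requires more lesions than CECT, for which Sample size assumes 90% sensitivity. Read per lesion, CEUS at 73% would find 3.67 × (0.90 − 0.73) = 0.62 fewer lesions per patient than CECT, and 82.5% is also below 90%. Steps 2 and 3 therefore speak only to the ultrasound half of the rule. The protocol's upper value for CEUS, 95%, exceeds 90%, so the CECT half is not out of reach, but it was not tested here.

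**5. The planned total of 330.** It cannot be uniquely reproduced, because the inputs are ranges and power is given as 80% or 90%. Across 1,080 input and formula combinations the total ran from 24 to 4,383, and 17 combinations came within 3% of 330. The point does not depend on this figure.

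**The case against.** Several objections have force.

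- **The lesion count serves a stated purpose.** The Introduction calls the number, size and location of metastases crucial to staging and treatment choice, and covers preoperative as well as follow-up patients. This stands. One might infer that the count is the wrong endpoint; the document does not support that, and the count can remain primary.
- **The trial could succeed entirely on known-positive patients.** A reader might infer this, but it cannot be shown. The share of such patients is stated nowhere, the entry wording is loose about what is known at enrolment, and the calculations leave out the CECT half of the rule. The Discussion's phrase "whether patients with a tentative diagnosis of liver metastasis could truly benefit" describes unconfirmed disease and is no evidence of known metastases.
- **Sensitivity will be overstated relative to follow-up screening.** This is also tempting, but nothing in the document supports it. In a within-patient comparison, easily seen lesions help every modality and may even dilute a CEUS advantage.
- **Accuracy measures are planned, and an analysis plan not shown may stratify.** This is true, and the lack of a subgroup analysis is not itself the fault. But the protocol itself fixes the success rule and its conclusion, and neither refers to those measures.
- **Readers work without clinical information.** This limits reading bias. It changes neither who is enrolled nor what is counted.
- **The 3.67 lesions per patient come from a small intraoperative series.** This stands. The figure is illustrative, and step 2 shows how much the answer moves with the assumed spread.

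**Conclusion.** The mismatch is in the text. Entry does not exclude known untreated metastases, the success rule is a pooled lesion count, and the conclusion attached to it is about screening. More lesions in already positive patients supports a detection or staging claim and leaves the screening claim unproven.

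The size cannot be fixed, because it depends on the unstated share of known-positive patients and on how lesions are spread over patients. The illustrations show only that a lesion gain need not bring a patient-level gain: 28% to 92% of simulated trials favoured CEUS over ultrasound with none at all, with CEUS at 73% on additional lesions. They rest on assumed lesion-count distributions and per-lesion sensitivities, and do not evaluate the comparison with CECT. The point should be corrected before analysis; it does not invalidate the primary endpoint.

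**What to change.** 1. Keep the lesion count as primary, and reword the conclusion under Primary endpoint so that success supports better lesion detection only.
2. Record at consent, before any study reading, whether liver metastasis is already known or reported on earlier imaging. Baseline and treatment history are already collected, so this may be only one more item on the case report form.
3. Tie any screening conclusion to a paired patient-level comparison in patients without known liver metastasis: at least one confirmed metastasis detected, yes or no, together with patient-level specificity.
4. Report patients with known metastases separately, as a detection or staging result.

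The cost is one form item, one further analysis and revised wording, with no additional imaging. The real downside is less precision for the screening claim, since it would rest on a smaller group of unknown size.

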### Schedule of the study

After obtaining informed consent, the study group will check both of the inclusion and exclusion criteria, participants' background and pregnancy status. Four training cases and 330 formal cases were included consecutively, and all subjects will be subjected to conventional ultrasound, Sonazoid-CEUS, CEMRI examinations, 65 of which should also be subjected to CECT examinations.

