### After inclusion

This study is divided into radiological examination (CECT/CEMRI) and ultrasound examination (conventional ultrasound and KPWLSM). Both parts are completed independently in a blind state of reading images and filling out the case report forms (CRFs). Either radiological or ultrasound examination start first is all right, and the interval between the two examinations is required from 24 h to 60 days.

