#### Radiological examination

Patients may have CECT/CEMRI tests before or after ultrasound, and the interval should be between 24 h and 60 days. After completion of the examination, the images will immediately acquire blind desensitization treatment to ensure blinded reading. Then two senior radiologists will evaluate the images blinded to the other imaging.

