### Data analysis

A commercially available software package (SAS version 9.2, SAS Analytics, Marlow, UK) will be used for all the statistical analysis, and the significance level was 0.05 for two-sided tests. Descriptive data will be mainly used in the study. Efficacy analyses of sensitivity, specificity, positive predictive value, negative predictive value and accuracy will be performed using the efficacy population including subjects who received Sonazoid-CEUS, conventional ultrasound, CECT and CEMRI in screening liver metastases.

For the comparison of superiority among Sonazoid-CEUS, conventional ultrasound and CECT, intra-individual comparison will be made in terms of the detection rate of the number of detected liver metastatic lesions with pared-samples *T*-test. And the Chi-square test or Fisher exact test will be used to compare the diagnostic accuracy of the three imaging modalities in screening liver metastases.

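### Entry to the CECT comparison subset is not protected from the Sonazoid-CEUS result, so the CEUS-versus-CECT comparison could be biased in either direction

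*Protocol article*

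**What the plan says.** Five statements in the Protocol article bear on this.

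- **Eligibility.** The Inclusion criteria section requires all four items, but the fourth is optional: patients "have done or plan to have a CECT examination within 2 months (optional, but at least 65 patients should finish it".
- **How the 65 are chosen.** The Schedule of the study section enrols the 330 consecutively and says of them only "65 of which should also be subjected to CECT examinations". It gives no rule for which patients these are.
- **Order of examinations.** Under After inclusion, either part may come first and "the interval between the two examinations is required from 24 h to 60 days". The Radiological examination section repeats this for CT and MRI: "Patients may have CECT/CEMRI tests before or after ultrasound, and the interval should be between 24 h and 60 days".
- **Analysis set.** The Data analysis section uses "the efficacy population including subjects who received Sonazoid-CEUS, conventional ultrasound, CECT and CEMRI in screening liver metastases". Membership follows from examinations received, not from a plan recorded at enrolment.
- **Blinding.** After inclusion says "Both parts are completed independently in a blind state of reading images and filling out the case report forms (CRFs". For radiology, "Then two senior radiologists will evaluate the images blinded to the other imaging". Both concern readers and forms. Neither covers the decision to obtain a CECT.

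**The concern.** A paired comparison of two tests is sound when entry to it does not depend on the result of either test. Here nothing secures that. A patient may enrol without a CECT plan, have the study ultrasound, receive a CECT within the next 60 days and be analysed in the CEUS-versus-CECT subset. Whoever decides on that CECT is not said to be unaware of the CEUS findings.

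The Primary endpoint section counts the study a success if Sonazoid-CEUS detects more lesions than conventional ultrasound and CECT, and the Secondary endpoint section compares diagnostic accuracy between CEUS and CECT. Both CECT comparisons rest on this subset, and it is small. At the 25–50% prevalence in the Sample size section, 65 patients contain about 65 × 0.25 = 16 to 65 × 0.50 = 33 with metastases. A 5-point difference in sensitivity is then about 1 to 2 patients, so a few CECTs added because of a CEUS finding could matter.

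**Working it through.** **The plan's own figure.** The only stated figure for this comparison is 65. It has no unique reproduction, because the AUC pair, the correlation and the prevalence used are not given and power is stated as 80% or 90%. One combination that reaches it is AUC 0.75 versus 0.95, prevalence 0.25, power 0.90 and correlation 0.7: 58 patients, and 58/0.9 = 64.4, rounded up to 65. The point below does not depend on this number.

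**Inputs from the Sample size section.** CECT sensitivity 90%; CEUS sensitivity 73–95% (85% used); CEUS specificity 65–75% (70% used); prevalence 25–50%.

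**Assumption, not in the documents.** r is the rate of CECT uptake in CEUS-positive patients divided by the rate in CEUS-negative patients. Values 0.5, 1, 1.5, 2 and 4 are shown. At r = 1 there is no bias.

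**Formulas, at patient level, if r applied to the whole subset.**

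- Apparent sensitivity = Se·r / (Se·r + 1 − Se)
- Apparent specificity = Sp / (Sp + (1 − Sp)·r)

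| r | Apparent CEUS sensitivity | Apparent CEUS specificity |
|---|---|---|
| 0.5 | 0.425/0.575 = 73.9% | 0.70/0.85 = 82.4% |
| 1 | 85.0% | 70.0% |
| 1.5 | 1.275/1.425 = 89.5% | 0.70/1.15 = 60.9% |
| 2 | 1.70/1.85 = 91.9% | 0.70/1.30 = 53.8% |
| 4 | 3.40/3.55 = 95.8% | 0.70/1.90 = 36.8% |

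CECT sensitivity stays at 90% if the tests are independent among diseased patients. Apparent CEUS sensitivity then reaches 90% at r = (0.90 × 0.15)/(0.85 × 0.10) = 1.59.

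**Correlated tests.** With correlation 0 to 0.3 among diseased patients and true CEUS sensitivity 84% (midpoint of 73–95%), CECT sensitivity also moves:

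- r = 2: CEUS 91.3%, CECT 90.0–91.8%, difference −0.5 to +1.3 points.
- r = 4: CEUS 95.5%, CECT 90.0–92.8%, difference +2.6 to +5.5 points.
- r = 0.5: CEUS 72.4%, CECT 87.2–90.0%, difference −14.7 to −17.6 points.

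The true difference is −6 points throughout.

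**Dilution.** Patients whose CECT was done or planned at enrolment keep the true 85%. If they made up half of the diseased patients in the subset, apparent sensitivity would be (85 + 95.8)/2 = 90.4% at r = 4 and (85 + 89.5)/2 = 87.2% at r = 1.5.

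**Accuracy.** Accuracy in the subset is a weighted average of the positive and negative predictive values, and r shifts weight between them. Accuracy therefore rises with r only where the positive predictive value is the larger.

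- Se 85%, Sp 70%, prevalence 25%, r = 4: (4 × 0.2125 + 0.525)/(4 × 0.4375 + 0.5625) = 59.5%, against a true 73.8%.
- The same with prevalence 50%: (4 × 0.425 + 0.35)/(4 × 0.575 + 0.425) = 75.2%, against a true 77.5%.
- Se 73%, Sp 75%, prevalence 50%, r = 4: (4 × 0.365 + 0.375)/(4 × 0.49 + 0.51) = 74.3%, against a true 74.0%.

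So the same referral pattern that raises CEUS sensitivity can lower or slightly raise its accuracy.

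**The case against.** The strongest reply is that the plan already ties CECT to enrolment. A CECT done or planned is an eligibility item, checked before the post-inclusion examinations. A patient who met it then cannot have entered the subset because of the study CEUS. On this reading, optional means only that patients without a CECT plan may also enrol, and the permission to scan after ultrasound concerns timing, not why a scan was ordered. This stands for patients with a CECT done or planned at enrolment. It does not cover patients enrolled without one, because the analysis set is defined by receipt and no statement excludes a CECT added later.

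Second, every patient has CEMRI, which the Discussion credits with excellent performance, so a new Kupffer-phase defect already has a further test ahead of it. This weakens the motive for an extra CECT but does not rule one out.

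Third, the article is condensed and its flow diagram is not visible, so the full protocol may designate the subset. That is possible. But the article itself states the entry rule, the order of examinations and the analysis set, and these as written leave the gap.

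A reader might go further and infer that CEUS sensitivity is inflated and that the ranking against CECT will be reversed in favour of CEUS on both endpoints. The documents do not support that. No statement says CEUS results trigger CECT, the direction depends on an unstated referral pattern, the 1.5-fold case leaves CEUS at 89.5% against 90% with no reversal, and the loss of specificity can work against CEUS on accuracy.

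**Conclusion.** The point holds as a gap in protection, not as a demonstrated bias. Optional CECT, permission to scan after the ultrasound and an analysis set defined by receipt together allow entry to the CEUS-versus-CECT comparison to depend on the CEUS result.

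Under preferential referral of CEUS-positive patients, a true sensitivity of 85% would read 89.5% (ratio 1.5) to 95.8% (ratio 4) against about 90% for CECT, and less when diluted by patients with CECT planned at enrolment. Under the opposite pattern it would read too low, for example 73.9% at ratio 0.5. The net effect on accuracy has no fixed sign.

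These sizes rest on assumed uptake ratios and on patient-level sensitivity, whereas the primary endpoint counts lesions and the secondary concerns a single lesion. They illustrate scale and do not predict the result. The gap still deserves closing, because primary success depends in part on this comparison and affected patients may not be identifiable later if order dates are not recorded.

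**What to change.** Define the CEUS-versus-CECT analysis set, and the count towards 65, as patients whose CECT was completed or already planned or ordered at enrolment, before the study ultrasound. Reword the fourth inclusion item to match, so that it is no longer both required and optional. Record the CECT order date on the CRF. Report CECTs added after the ultrasound separately, outside the primary and secondary CEUS-versus-CECT comparisons.

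This costs about one sentence in the inclusion criteria, a matching line in the Data analysis section and one CRF date. It leaves the target of 65 unchanged and does not restrict which scans a patient may have. The downside is that the 65 may accrue somewhat more slowly, because CECTs added after the ultrasound no longer count.
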